## 1. INTRODUCTION

Scoliosis is a 3-dimensional deformity characterized as a lateral curvature of the spine in the coronal plane as measured by Cobb angle  $>10$  degrees on plain radiographs. Patients with adolescent idiopathic scoliosis (AIS) may develop curve progression if left untreated, which can result in back pain, cosmetic disfigurement and early death from cardiopulmonary compromise.[1] The most common form of scoliosis is idiopathic and is usually detected during adolescence (10-18 years of age).[2] Based on the investigators' large-scale and internationally renowned Hong Kong-based scoliosis school screening program [3, 4], the prevalence of spine curvatures were as follows:  $\geq 10$  degrees was 2.2% for boys and 4.8% for girls;  $\geq 20$  degrees was 0.7% for boys and 2.8% for girls; and for  $\geq 40$  degrees the prevalence was 0.1% for boys and 0.4% for girls.[3] It is important to note that approximately only 78% of students in Hong Kong have participated in the school screening system. Hence, the prevalence may perhaps be an underestimation. Currently, in Hong Kong, all children diagnosed with AIS and noted to have a  $\geq 20$  degrees curve are referred to one of two scoliosis clinics for management as those who are skeletally immature have potential to deteriorate during growth and may be treated by bracing.[5] To place into context the magnitude of service required, "450-500 new braces" are prescribed per year in our clinic alone.

Bracing is the most common treatment method for controlling AIS progression and its main purpose is to prevent curves from reaching the surgical threshold of  $>50$  degrees. However, prevention of any Cobb angle progression is also beneficial. Normally, at the end of skeletal growth, there is a significant reduction in risk of further curve progression. However, there is an increased risk of continued progression into adulthood of at least 1 degree per year for curvatures of  $\geq 40$  degrees at skeletal maturity. Hence, not only is a smaller Cobb angle at skeletal maturity more cosmetically acceptable, preventing the 40 degree threshold can reduce the risk of adulthood deterioration and surgery as suggested by natural history studies.[1, 6] Good brace compliance with more than 20 hours of daily use is proven to be effective in reducing curve progression.[7] High-level and established evidence have been published which support its efficacy.[8-10] Specifically, Weinstein et al[9] have demonstrated in a multicenter study that in patients with high-risk curves bracing significantly decreased curve progression and the need for surgery. Based on that study,

longer brace wearing decreased curve progression and the need for surgery.

At the end of skeletal growth, treatment is completed and braces are removed or “weaned”.[7, 11, 12] This decision should be made in a timely fashion as drawbacks and complications have been noted with prolonged brace use. Prolonged bracing in children may reduce spinal mobility, lead to poor body image and self-esteem, and worsen quality of life.[13-18] There is a risk of osteoporosis and the prevalence of low bone mineral density in AIS patients may involve up to 38% of individuals.[19] A major reason why osteoporosis may occur is the reduced physical activity and use of core musculature due to brace immobilization. Although bracing improves trunk posture, it limits active body movement.[20] In the long-term, reduced spinal mobility and muscle endurance may occur up to 20 years after bracing has completed.[21] We currently have accurate parameters that help determine when patients reach skeletal maturity and no longer require further bracing.[22] However, **the manner in which brace treatment should be weaned is “clinician-dependent” and without any supporting evidence.**

For brace weaning, AIS patients can only rely on the surgeon’s decision rather than evidence-based guidelines. This may be a **slow weaning process**, whereby the duration of brace wear is slowly reduced or changed to night-use only, or may be a **rapid immediate removal** of the brace. The main rationale for a slow gradual weaning process over a period of at least 6 months is to allow the spine to adapt to an environment without loading by the brace while maintaining the corrective posture. We postulate that by this method, the curve magnitude measured by the Cobb angle and the overall truncal balance and posture may be maintained even after brace removal. The resulting curve magnitude is the commonly used outcome measure of treatment as it has bearing on the likelihood of curve deterioration and surgery. However, truncal balance may be a larger concern for patients due to its larger impact on overall cosmesis. Whether this theory of gradual weaning benefits holds true is unknown but is supported by our knowledge of the spine’s viscoelastic properties. The viscoelasticity of spinal structures including the ligaments, joint capsules and intervertebral discs allows deformation changes while loading and unloading the spine.[23] A lag-time response of spinal soft tissues to these changes have been demonstrated. Despite our limited knowledge on the effects of gradual weaning on the spine, deterioration in Cobb angle and truncal balance parameters may lead to worse cosmesis and quality of life, and possible need for surgery. Hence, **lack of an optimal brace weaning protocol is a significant**

## **limitation in our current management of AIS patients.**

In this modern era, there is increasing emphasis placed on evidence-based health-care. Clinicians and health-care administrators are tasked to provide the best care for our patients. While some clinicians may terminate brace treatment with a gradual weaning period, others are content with immediate brace removal to avoid prolonged brace treatment. Due to the lack of evidence for either method, it is an appropriate time to determine any advantages of gradual brace weaning for AIS patients. Bracing is a commonly used tool for preventing curve progression, and it is imperative to deliver the best treatment protocol to these children. With this purpose, we propose a randomized controlled trial to determine whether gradual weaning does benefit over immediate weaning.

## **2. STUDY OBJECTIVES**

### **a. Primary Aim**

To compare the degree of Cobb angle maintenance between immediate removal and gradual brace weaning protocols for AIS patients at 1 year after brace weaning.

Our hypothesis is that gradual brace weaning allows better adaptation to an unloaded environment without the brace in AIS patients, thereby resulting in better maintenance of the Cobb angle at 1 year after brace weaning.

### **b. Secondary Aim**

i. To compare the degree of truncal balance maintenance between immediate removal and gradual brace weaning protocols for AIS patients after brace weaning.

We hypothesize that AIS patients with gradual brace weaning allows better adaptation to an unloaded environment without the brace thereby resulting with better maintenance of

truncal balance.

ii. To determine any differences in health-related quality of life (HRQOL) between immediate removal and gradual weaning protocols.

We hypothesize that due to improved Cobb angle and truncal balance maintenance, the HRQOL is better for the gradual weaning protocol.

### **3. STUDY DESIGN**

#### **a. Overall Study Design**

This is an open-labelled, randomized controlled trial for testing two brace weaning protocols, namely immediate removal of brace to that of gradual brace weaning over a course of 6 months and followed-up for 12 months and 24 months. The Clinical Trials Centre (CTC) at the University of Hong Kong is involved in reviewing the study design, statistical methodology of the concept, sample size calculation and will also aid in data and study site monitoring after study commencement.

#### **b. Definition of Study Intervention**

As there is no definition for “brace weaning”, we adopt the protocol that our center has been using which has also been previously published.[24] Hence, we will be comparing two groups:

1) gradual brace weaning with the brace wearing time shortened to night wearing for 6 more months before stopping bracing altogether or

2) immediate brace weaning on the day of patient recruitment.

### **c. Study Duration**

All subjects will be followed-up longitudinally the primary end point at 1 year after brace weaning has been issued. A final assessment time point at 24 months is added to assess the long term efficacy [25] of weaning protocol in the maintenance of curve magnitude and truncanal balance. Therefore, this includes three clinic visits with one at 6 months to complete the gradual brace weaning protocol, another at 1 year and a final visit at 2 years to observe for any delayed changes to the overall curvature and balance, including loss of truncanal balance and Cobb angle deterioration. This follow-up duration is based on previous work suggesting that the highest risk of post-brace weaning curve progression occurs within 6 months of stopping brace wear.[24] A 1-year collection of data is adequate for seeing differences between the two groups. This does not deviate significantly from our usual care as all AIS subjects in our clinic are followed-up at 6-monthly intervals. The 2 year visit will offer additional information about the effects of brace weaning protocols in the long term.

## **4. STUDY POPULATION**

We will recruit AIS patients managed at the Duchess of Kent Children's Hospital (DKCH) in Hong Kong. DKCH is one of two only scoliosis centers in Hong Kong that manages AIS. Being under the same umbrella of the Hong Kong healthcare system, the data gathered at DKCH is representative of the whole of Hong Kong with regards to the same referral, treatment protocol and healthcare cost system.

### **c. Inclusion Criteria**

A patient will be eligible for study participation if he/she meets all the following criteria:

- All AIS patients treated with underarm (Boston) bracing who are ready to undergo brace weaning
- Primary curve ranging between 20 and 40 degrees of Cobb angle measurement

- Have reached skeletal maturity based on the Scoliosis Research Society (SRS) standardized criteria: Risser stage  $\geq 4$ ,  $>2$  years post-menarche, and no growth between 2 visits.

#### **d. Exclusion Criteria**

A patient will be excluded from the study if he/she meets any of the following criteria:

- Non-AIS patients
- Those undergoing Milwaukee bracing
- Patients who undergo brace weaning not because of skeletal maturity but because of the need for surgical intervention
- Cognitively impaired, unable to comply with study follow-up and protocol issued
- Refused consent for study.

## **5. RANDOMIZATION AND ALLOCATION**

Block randomization with randomly selected even number of block sizes will be used to ensure a balance in sample size between the study groups. A master randomization list will be generated by a statistician a priori. A web-based randomization application will be set up and the randomization list will be uploaded. Using the application, eligible patients who have consented to take part in the study will be randomly allocated to one of the two protocols by the project coordinator. The master randomization list will be managed independently by the project coordinator and concealed to all research staff until the study database closure. Attending specialist will perform patient recruitment and informed consent procedure. Project coordinator will be responsible for allocating recruited patients to either of the two arm of the trial.

## **6. STUDY ASSESSMENTS**

All subjects will undergo weight, standing and sitting height, and arm span measurements, HRQOL and utility measurements, and whole spine standing posteroanterior (PA) and lateral radiographs at each clinic visit. The refined Scoliosis Research Society 22-item (SRS-22r) questionnaire and the EuroQoL 5-Dimension 5-Level (EQ5D) questionnaire will thus be provided at every visit for HRQOL and utility assessment. For all patients undergoing bracing, an orthotist assessment is also performed at each clinic visit for any brace modification and education. Further details regarding the measurements assessed are listed in the following pages.

### **Study Outcomes**

#### **a. Primary outcome**

- Change in Cobb angle from baseline to 6 months, 1 year and 2 years follow-up.

#### **b. Secondary outcomes**

- Change in truncal balance from baseline to 6 months, 1 year and 2 years follow-up.
- SRS-22r total score at 6 months, 1 year and 2 years follow-up.
- EQ-5D utility score at 6 months, 1 year and 2-years follow-up.

### **Study Measurements Assessed**

#### **1. Socio-demographics**

These data include the date of birth, gender, ethnic group, school grade, the number of siblings and siblings also under scoliosis management.

#### **2. Body size and maturity parameters**

This includes standing and sitting height, weight, and arm span at each follow-up

visit. All of these clinical parameters are measured routinely and hence, the height change since the previous follow-up can be measured. For girls, the menarche status and the start date of menarche will also be extracted. The Risser sign is determined by evaluating the extent of ossification of the iliac apophysis on the same PA spine radiographs used to assess the spine radiographic measurements. The bone age by the distal radius and ulna classification [22] will also be measured on left hand radiographs at each visit. These maturity status indicators are used to determine whether a patient is ready for brace weaning.

### 3. Scoliosis specific parameters

All AIS patients at DKCH will have standing PA and lateral whole spine radiographs taken at each follow-up visit with the EOS® (biplanar x-ray system); from which, the curve type (i.e. double primary, thoracic, thoracolumbar, and lumbar, according to the SRS Spinal Classification Nomenclature), number of curves, coronal Cobb angle, and apex will be assessed. Additional data regarding balance parameters include clinical rib hump (apical trunk rotation) measurement by scoliometer (measured routinely by a designated clinic nurse), radiological measurements of the T1 tilt, shoulder height, truncal shift, listing (C7-central sacral vertebral line deviation), sagittal vertical axis, lumbar lordosis (L1-S1) and thoracic kyphosis (T5-12). For all radiographic parameters, the two independent investigators will perform all measurements independently. When the difference in measurements are less than 5 degrees or 5mm, the mean of the two measurements will be taken and reported on the source document. When the discrepancy is more than 5 degrees or 5mm, the two assessors will meet and discuss, and come up with a joint concluded value for reporting.

### 4. Mode of treatment

Data to be retrieved include the duration of brace treatment, as well as the corresponding start and end dates. Any previous complications from bracing including curve deterioration, abrasions and bruising will be recorded.

### 5. Brace compliance and routine measures for the gradual bracing group

All subjects undergoing gradual brace weaning will have thermal sensors to monitor

compliance to our weaning protocol. An additional orthotic assessment will be performed as usual prior to clinic consultation to scan the sensor for compliance data. This will be considered in any cost-utility assessment. To standardize the taught physical activity between the two groups, no additional physiotherapy sessions will be arranged for scoliosis specific exercises.

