### 1. PRIMARY ANALYSIS

The primary analysis will be evaluated by two independent sample *t*-test to determine the significance of the differences in change of Cobb angle and truncanl balance

between the two groups. The analysis will primarily be carried out according to intention-to-treat (ITT) and subordinately based on per-protocol (PP) principle. The ITT analysis will include any randomized patients with non-missing efficacy measures. The PP analysis will include all randomized patients in ITT who fulfil the criteria of PP population.

The PP population is defined as a subset of the ITT population. Patients will be included in the PP population if they have:

- no late report violations of entry criteria,
- no incorrect treatment group assigned,
- no major protocol deviation(s) that is/are clinically significant to efficacy outcome,
- no treatment during follow-up after weaning, and
- with sufficient treatment compliance.

Sufficient treatment compliance is defined as gradual brace weaning patients having completed at least 8 hours/night of brace-wear for >80% of the 6-month gradual weaning period. Brace-wear compliance (hours/day) for the 6-month gradual weaning period will be recorded by thermal sensor.

Both ITT and PP results will be reported for primary analyse.

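### Brace wear is systematically measured only in the gradual arm and only for its 6-month weaning period, so per-protocol exclusions are asymmetric and any night wear in the immediate arm goes unquantified

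*Supplement*

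**What the plan says.** Protocol section 3b defines the arms. One is "gradual brace weaning with the brace wearing time shortened to night wearing for 6 more months before stopping bracing altogether or" the other, "immediate brace weaning on the day of patient recruitment". Section 3a describes the design: "This is an open-labelled, randomized controlled trial for testing two brace weaning protocols".

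Measurement of wear appears in protocol section 6, item 5, whose heading names the gradual group only: "All subjects undergoing gradual brace weaning will have thermal sensors to monitor" adherence to the weaning protocol. Table 1 has one wear item, hours by thermal sensor. The orthotist assessment in section 6 is for patients who are undergoing bracing. Item 4 (Mode of treatment) retrieves the duration of brace treatment with start and end dates, without restriction to one arm.

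The SAP, under Primary Analysis, limits the sensor record: "Brace-wear compliance (hours/day) for the 6-month gradual weaning period will be recorded by thermal sensor". Compliance is defined for one arm: "Sufficient treatment compliance is defined as gradual brace weaning patients having completed at least 8 hours/night of brace-wear for >80% of the 6-month gradual weaning". Two further PP criteria are not limited by arm: "no treatment during follow-up after weaning, and" and "no major protocol deviation(s) that is/are clinically significant to efficacy outcome". For neither does the SAP give a data source, a method or a threshold. ITT is the primary analysis and PP is subordinate; both are to be reported.

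**The concern.** Brace wear is the experimental contrast. A trial of this kind should be able to show, for both arms, how far the assigned condition was delivered. Here that is possible for the gradual arm during six months and not otherwise.

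Two things are at stake. First, the PP set. A gradual-arm patient who wears the brace too little is identified by sensor and removed. An immediate-arm patient who continues night wear is removed only if somebody happens to notice or the patient volunteers it. The PP comparison then sets a group filtered on measured adherence against one that is hardly filtered.

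Second, the reading of a small or null difference. Patients know their allocation, and those in the immediate arm come into the trial with a Boston brace. Any who continue night wear receive something close to the comparator. If bracing has an effect, that moves the ITT difference towards zero. Without a count of such patients, a null result could mean that the two methods give similar outcomes or that the contrast in brace wear was smaller than planned.

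**Working it through.** **Step 1. Where could brace use come to light?**

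| | Gradual arm | Immediate arm |
|---|---|---|
| Months 0 to 6 | Thermal sensor, hours/day; PP threshold defined | No sensor, diary or question described; no adherence definition |
| After month 6 | Sensor period over; no question described | No question described |
| Brace end date (protocol section 6, item 4) | Retrieved | Retrieved |
| PP exclusion for post-weaning treatment | Applies; source not stated | Applies; source not stated |
| PP exclusion for major deviations | Applies; source not stated | Applies; source not stated |

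The end date and the two PP exclusions are routes by which reported brace use could be recorded. They do not measure it. A date does not give nights or hours, and item 4 also speaks of previous complications, so it reads at least partly as treatment history.

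**Step 2. Inputs for the dilution illustration.** From the SAP sample size section: difference 2 degrees, SD 6 degrees, alpha 0.05, 154 per group recruited, 20% attrition at 1 year. Number analysed per arm: 154 × 0.8 = 123.2, taken as 123. Assumptions not in the documents: a two-sided test (sidedness is not stated), a crossover share c in the immediate arm, and the full effect of night wear in crossovers.

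**Step 3. The plan's own figure.** The SAP gives 128 per group for 80% power. On its inputs a two-sided t-test needs 143 per group (solution 142.2), and 128 per group gives power 0.757; a one-sided test needs 112. So 128 is not reproduced. That is a separate matter. It is noted here because the illustration starts from 0.74 instead of 0.80 for that reason and because of attrition; only the fall below 0.74 belongs to crossover.

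**Step 4. Dilution.** If a share c of the immediate arm behaves as the gradual arm, the expected ITT difference is 2 × (1 − c). The standard error is 6 × √(2/123) = 0.765. Power is from the noncentral t distribution with 244 degrees of freedom.

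| c (assumed) | Difference | Difference / SE | Power |
|---|---|---|---|
| 0 | 2.0 | 2.61 | 0.740 |
| 10% | 1.8 | 2.35 | 0.649 |
| 20% | 1.6 | 2.09 | 0.549 |
| 30% | 1.4 | 1.83 | 0.445 |

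With 128 analysed per arm the powers are 0.757, 0.667, 0.566 and 0.460.

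**Step 5. Partial effect.** If crossovers gain only half the effect, the difference is 2 × (1 − 0.5c). For c = 10%, 20% and 30% that gives 1.9, 1.8 and 1.7 degrees, and power 0.70, 0.65 and 0.60 with 123 per arm.

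**Step 6. Direction.** The dilution applies to immediate-arm wear. Gradual-arm wear beyond month 6 would, if bracing helps, widen the difference; it does not pull the arms together. It is equally unmeasured, but its effect runs the other way.

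**The case against.** The strongest reply is that the plan already provides for this. The PP set excludes patients treated after weaning and those with major deviations, in either arm; brace end dates are retrieved; and every patient is seen at 6, 12 and 24 months. This stands in part. A reader might infer that crossover could never be detected. The documents do not support that: brace use that is volunteered or noticed can be recorded and acted on. What remains is that no method or threshold is named, while the gradual arm has a device and a numerical rule.

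A second reply is that ITT is primary and compares the two instructions whether or not they are followed. This stands fully. A reader might infer that unmeasured crossover invalidates the primary comparison, or leaves a null result without meaning. It does neither: a null ITT result still answers the practical question of which instruction to give. What it cannot settle alone is whether brace wear itself makes no difference, which is closer to the hypothesis about adaptation to an unloaded spine in protocol section 2a.

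A third reply is that crossover is conjecture. This also stands. The documents do not say that immediate-arm patients keep their brace or wish to wear it, and the introduction lists drawbacks of prolonged bracing that would make many glad to stop. The rates in the illustration have no source in the documents.

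**Conclusion.** The point holds as a gap in ascertainment. Brace wear is systematically measured in one arm for six months; in the immediate arm, and in both arms after month 6, the plan names no way of finding it out. The PP criterion on post-weaning treatment therefore cannot be applied equally, and any dilution of the ITT difference cannot be quantified.

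The size of the dilution is unknown. Under assumed immediate-arm crossover of 10% to 30% with full effect, 2 degrees becomes 1.8 to 1.4 and power falls from 0.74 to between 0.65 and 0.45; with half effect the loss is smaller. The sample size makes no allowance for crossover. The validity of ITT for the two instructions is not in question, so this is a cheap improvement to data collection and interpretation.

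**What to change.** At the existing 6-, 12- and 24-month visits, ask every patient in both arms the same question on brace use since the last visit: none, nights per week, approximate hours. In the SAP, name this item as the source for the existing PP criteria on post-weaning treatment and major deviations, state the threshold and the date from which each criterion runs in each arm, and apply them identically. Report crossover by arm beside the primary result. Keep the sensor record for the gradual arm as planned.

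The cost is one case-report-form item at visits that already take place. The drawback is reliance on self-report, which in an open-label trial may understate departures from the allocated protocol. Asking in both arms at least gives one common source, and in the gradual arm the answers for the first six months can be compared with the sensor.
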